### Prior and Concomitant Medication

The participants will be instructed to not take medications other than the trial drugs for any disease without consulting the investigators. The investigator will instruct the participants to consult them for any other signs and symptoms or if anything unusual occurred. The investigator will record any other medications the participants took.

### Rescue Medication

Rescue medication will be used to alleviate any emergency condition at the investigator’s discretion and will be documented in detail in the CRF.

## Results

The project was funded by the CCRAS in February 2023. Participant recruitment was initiated on September 22, 2023. As of May 2024, we enrolled 72 participants in both groups. Data analysis will be completed by February 2025, and the results will be published afterward.

## Discussion

### Conclusions

Ayurveda scholars correlate AR with types of diseases (pratishyaya/pinasa; National Ayurveda Morbidity Code: I-1) based on the similarities in causes, clinical features, and treatment. This paper describes the protocol for the Ayurvedic management of AR. We undertook a randomized controlled trial to objectively assess the efficacy of Ayurvedic treatments for the management of AR and compared it with the gold standard intranasal corticosteroids for mild to moderate AR. We assessed the changes objectively by using the CARAT score and nasal endoscopy index as the outcomes for participants with AR.

The literature suggests that, based on the severity of the disease and condition of the patient, Ayurveda has multiple treatment modalities for this ailment, including Shodhana Karma (biocleansing therapy; Standard Ayurveda Terminology [SAT]: I.76) and Samshamana (palliative procedure; SAT: I.37) [23]. The primary treatment modality for managing diseases of the head and neck is Nasya (medication through the nasal route; SAT I.156). Most Ayurveda drugs and preparations used for the treatment of AR have been proven to have immunomodulatory, antiallergic, and anti-inflammatory properties [24]. Studies have demonstrated promising results of some Ayurveda interventions for managing AR. With this study, we aim to observe the effectiveness and safety of Ayurvedic management using the formulations of NLR, Shirishadi Kwath, and Anu Taila Nasya in reducing symptoms associated with AR, such as rhinorrhea, nasal itching, paroxysmal sneezing, nasal congestion, and obstruction. If beneficial, this study could contribute significantly to integrative approaches for managing AR.

### Strengths and Limitations

The strengths of this study include its randomized design and inclusion of enough participants to allow for adequate statistical power for subgroup analyses. This study uses the CARAT score and nasal endoscopy index, which are well-validated instruments to assess AR.

One potential limitation of this study is that the investigators were aware of the participants’ group assignment, and therefore, bias in favor of any particular group cannot be excluded. However, every effort was made to ensure blinding of the participants during the group allocation. An independent evaluator blind to study conditions was responsible for administering all study measures. A second limitation is the short intervention of the trial (ie, 45 days). However, the study follow-up was longer (ie, 90 days) to assess the recurrence of the symptoms/disease.

The results are expected to show better relief for AR for the treatment group. The protocol may also serve as a reference for the planning of similar clinical trials*.*

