**Methods:**

This ongoing study is an open-label randomized controlled interventional trial, with a sample size of 90 both in the trial and standard control group (including dropouts, 20%), and will be carried out for 24 months. Participants in the trial group will receive Ayurvedic treatment, that is, Anu Taila Nasya (6 drops in each nostril for 7 days for 3 consecutive weeks), Naradiya Laxmivilas Rasa (250 mg twice per day), and Shirishadi Kwath (40 ml twice per day for 45 days). The participants in the control group will receive a fluticasone propionate nasal spray (2 sprays once per day for 45 days). The primary outcome will include the mean change in the Control of Allergic Rhinitis and Asthma Test score, and the secondary outcomes will include the mean change in the nasal endoscopy index (assessment of nasal membrane color, pale or hyperemia; rhinorrhea, watery or yellow; and inferior turbinate swelling, hypertrophy) and the mean change in the laboratory tests.

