### Sample Size

In a previous pilot study on this Ayurvedic intervention, a change of 14 points in the CARAT score was observed. For this study, it was assumed that a change of 10 points would be seen in the placebo group. With an SD of 6 points based on the results of the previous pilot study, a sample size of 35 participants per group was calculated to provide 80% power, with a 95% CI.

Assuming a dropout rate of 20%, a total of 90 participants, 45 per group, will be included in this trial.

n_1_ = n_2_ = 2 *σ*^2^ [(Z_1 – α/2_) + (Z_β_)]^2^ ÷ Δ^2^

n_1_ = n_2_ = 2 * (6)^2^ [(1.96 + 0.84)]^2^ ÷ (4)^2^

n_1_ = n_2_ = 35

where Δ is |μ_2_ – μ_1_| (the absolute difference between two means), σ is the variance of two means, n_1_ is the sample size for group 1, n_2_ is the sample size for group 2, α is the probability of type 1 error (usually .05), β is the probability of type 2 error (usually .2), and z is the critical *Z* value for a given α or β.

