### Randomization and Allocation

A randomization chart has been generated with the help of computer-generated random numbers. Participants will be randomized in a ratio of 1:1 to either the study group or the control group. The randomization schedule will be strictly controlled and remain with the biostatistician/data analyst. Sequentially numbered, sealed, opaque envelopes will be used to conceal the allocation.

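### The claimed strength of adequate power for subgroup analyses is contradicted by the trial's own sample size calculation, and the remark on participant blinding needs reconciling with the open-label design

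*Protocol article*

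**What the plan says.** **Power.** Strengths and Limitations names as a strength the "inclusion of enough participants to allow for adequate statistical power for subgroup analyses". In Sample Size, "a sample size of 35 participants per group was calculated to provide 80% power" for a single two-group comparison of CARAT change. After a 20% dropout allowance, "a total of 90 participants, 45 per group, will be included in this trial". No subgroup is defined in the article, and Statistical Methods describes no subgroup analysis.

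**Blinding.** The Abstract states: "This ongoing study is an open-label randomized controlled interventional trial". Study Interventions describes a nasal therapy plus two oral products in one arm and a nasal spray in the other, with no dummy treatment. The limitations paragraph concedes that investigators knew the assignment and that bias cannot be ruled out. It then says that all efforts were made to blind participants at the time of group allocation, and adds: "An independent evaluator blind to study conditions was responsible for administering all study measures". Randomization and Allocation describes sealed opaque envelopes, which is concealment of the sequence; no procedure for masking participants is given.

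**The concern.** The trial was sized to just reach 80% power for its overall comparison. A subgroup is a fraction of that sample, so at the same effect and SD its power must be lower. Testing whether the effect differs between subgroups needs more patients still. A reader who accepts the stated strength could take a non-significant subgroup result as evidence of no effect, or treat a difference between subgroups as something the trial was built to detect. The article also offers itself as a reference for planning similar trials, so the statement may be carried forward.

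The blinding remark raises a smaller issue. CARAT, the primary outcome, asks about symptoms, sleep and activity limitation, so its answers come from the patient. In an open-label trial with visibly different regimens, the patient knows the treatment. A reader could take the remark on participants, together with the blind evaluator, to mean that the primary outcome is protected from expectation.

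**Working it through.** **Inputs**
- Treatment arm: "a change of 14 points in the CARAT score was observed" (Sample Size).
- Comparator: "it was assumed that a change of 10 points would be seen in the placebo group" (Sample Size). The difference is therefore Δ = 14 − 10 = 4.
- σ = 6 and dropout 20% (Sample Size).
- Two-sided α = 0.05 (Statistical Methods).
- Allocation 1:1 (Randomization and Allocation).
- Subgroup shares of one half, one third and one quarter are assumptions, because the article defines no subgroup.

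**Step 1: reproduce the plan's figure.** n = 2σ²(1.96 + 0.84)²/Δ² = 2 × 36 × 7.84/16 = 35.28 per group, stated as 35 (36 if rounded up). With dropout, 36/(1 − 0.20) = 45 per group, 90 in total. The stated total reproduces.

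**Step 2: overall power.** With n per arm, SE = 6√(2/n), and power is taken from the noncentral t with noncentrality 4/SE (normal approximation in brackets):
- 35 per arm: 78.5% (79.6%)
- 36 per arm: 79.7% (80.7%)
- 45 per arm, no dropout: 87.9% (88.5%)

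After the planned dropout, no power is left over.

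**Step 3: power inside a subgroup.** The same formula is used with k = share × n per arm. For one half of 36, k = 18, SE = 6√(2/18) = 2.00 and 4/SE = 2.00.

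| Share of patients | 36 evaluable per arm | 45 per arm, no dropout |
|---|---|---|
| One half | k = 18: 49% (52%) | k = 22.5: 59% (61%) |
| One third | k = 12: 35% (37%) | k = 15: 42% (45%) |
| One quarter | k = 9: 26% (29%) | k = 11.25: 33% (35%) |

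By the formula in step 1, 80% power inside a subgroup needs about 36 patients per arm in that subgroup. That is every evaluable patient after the planned dropout, or 36/45 = 80% of all patients if nobody drops out.

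**Step 4: power for an interaction.** For two equal halves with k per arm in each, SE = 6√(2/k + 2/k) = 6√(4/k).
- 36 per arm: SE = 6√(4/18) = 2.83. Power for a 4-point interaction is 29%. The interaction detectable with 80% power is 2.80 × 2.83 = 7.9 points.
- 45 per arm: SE = 6√(4/22.5) = 2.53. Power is 35%. The detectable interaction is 2.80 × 2.53 = 7.1 points.

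These use the normal approximation; the t distribution changes them only slightly (28.6% and 34.6%; 8.0 and 7.2 points). For 80% power on a 4-point interaction, n per arm = 4 × 2 × 36 × (1.960 + 0.842)²/16 = 141.3, so about 142 evaluable per arm.

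**Step 5: the blinding sentences, side by side.** An open-label design with different routes and numbers of products, and no dummy, means that participants know what they receive once treatment starts. The remark about participants is limited to the moment of allocation, and the only procedure described for that moment is the sealed envelopes. The two statements fit together if the remark means allocation concealment, but the text does not say so. The blind evaluator is described as separate from the investigators, and nothing elsewhere contradicts this. An evaluator's blindness does not change what an unblinded patient answers about symptoms.

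**The case against.** **No subgroup analysis is planned.** The article defines none, the claim sits in the discussion, and neither the sample size nor the primary analysis depends on it. This stands as a limit on the harm: over-reading is a risk only if subgroup analyses are done. It does not rescue the claim, which is a positive statement about power that the article's own inputs refute.

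**The shares are the reviewer's.** True, which is why a range is shown. An equal split is among the kinder choices, and smaller subgroups do worse.

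**The Abstract's wording of the sample size could be read as 90 per arm.** Sample Size settles it as 90 in total. On the other reading a half-size subgroup would reach about 88%, but one third would reach 72%, one quarter 59%, and a 4-point interaction 61%.

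**A reader might infer that blinding is also claimed as a strength, and falsely.** The article does not support that. The blinding sentences stand in the limitations paragraph, after the admission that bias cannot be excluded. The participant remark is qualified by its reference to allocation and may loosely describe the envelopes. A blinded assessor is compatible with an open-label trial, so there is no ground for asking that the evaluator statement be withdrawn or confined to endoscopy. Nor can an inflated type I error be given: the article supports neither a size nor a direction for expectation bias, and with an active comparator it could favour either arm.

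**Conclusion.** The claim of adequate power for subgroup analyses is wrong by the protocol's own calculation. At the planned 4-point effect and SD 6, the assumed subgroups of one half to one quarter have about 26% to 59% power across the dropout range. A 4-point interaction between equal halves has about 29% to 35%, and only an interaction of about 7 to 8 points, nearly twice the planned main effect, would be detected with 80% power. These figures assume the planned SD in every subgroup, equal shares across arms, and 36 to 45 analysed patients per arm.

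On blinding, the conclusion is narrower. The participant remark is unclear beside the open-label label and should be reconciled with it. The limits of a blind evaluator for a patient-answered primary outcome should also be stated. The evaluator statement itself is not contradicted.

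**What to change.** - In Strengths and Limitations, delete the clause on subgroup power and state that the trial is powered for the overall comparison only.
- State that any subgroup analysis is exploratory, reported as an interaction estimate with its 95% CI and without efficacy claims.
- Reconcile the remark on participants with the open-label design. If allocation concealment is meant, say so and refer to the sealed envelopes.
- Add one sentence that CARAT is answered by patients who know their treatment, so a blind evaluator does not remove expectation bias from the primary outcome. Keep the blind-evaluator statement.

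The cost is wording only. One claimed strength is withdrawn; the design, sample size and conduct are unchanged.

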## Appendix

Multimedia Appendix 1 Control of Allergic Rhinitis and Asthma Test.

Multimedia Appendix 2 Nasal endoscopy index for patients with allergic rhinitis.

## Abbreviations

AR: allergic rhinitis
ARIA: Allergic Rhinitis and Its Impact on Asthma
CARAT: Control of Allergic Rhinitis and Asthma Test
CCRAS: Central Council for Research in Ayurvedic Sciences
CONSORT: Consolidated Standards of Reporting Trials
CRF: case report form
NLR: Naradiya Laxmivilas Rasa
SAT: Standard Ayurveda Terminology
SPIRIT: Standard Protocol Items: Recommendations for Interventional Trials
